Despite the pervasive use of wheelchairs as an intervention in rehabilitation, the evidence for training in effective wheelchair use is still underdeveloped. *Structured* *training* has demonstrated excellent potential, but the most effective and efficient means of providing that training remains unclear. Larger multi-site clinical trials are required to establish evidence to inform and direct clinical practice. We propose that this 2-year feasibility trial is not only **critical, but also prudent, prior to moving forward** with an expensive large multi-site randomized controlled trial (RCT). Specifically the results of this study will address 1) **feasibility outcomes** (i.e., recruitment and retention; trainer and subject burden; safety; intervention administration and adherence; perceived benefit) and 2) **clinical outcomes** (i.e., effect size calculations for the primary and secondary measures). Although the principal intent is feasibility, our sample size calculation is based on the primary clinical outcome to provide a reasonable estimate of an effect size for planning the subsequent large scale RCT.

**HYPOTHESES:** We expect that the **feasibility outcomes will be sufficiently robust to support conducting a subsequent multi-site RCT.** We also expect the EPIC WheelS training program will have **a significant treatment effect** with improvement in wheelchair mobility, compared to a control group**.** The primary **clinical** endpoint will be wheelchair skill *capacity*, as measured by the Wheelchair Skills Test (WST). Secondary clinical outcomes will include wheelchair skill *safety*; confidence with wheelchair use; mobility; and user evaluation of performance in participation-oriented activities.

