**3. Structured skills training is effective, but currently relies on considerable 1:1 training time.**

The Wheelchair Skills Training Program (WSTP)^14^ is the only *structured* training program reported in the literature. An expert clinician provides personal training in a clinical (hospital) setting, typically requiring 4 to 8 sessions. Several studies have demonstrated the WSTP to be safe and practical^15, 16^ and randomized controlled trials report a significant improvement in skill capacity among adult MWC users during inpatient rehabilitation^17^ and in the community^18^ [15-20% in intervention groups versus 3-8% in control groups on the WST]. More recently, a Turkish study also found comparable improvement in *safety* with skill performance.^19^ However, these studies required that either the subject travel to the training facility or the clinician travel to the home for all training. While frequent and intensive 1:1 training with an expert clinician may be optimal, therapists do not have the time or resources to offer this level of service. Therapists typically introduce wheelchair skills sporadically during rehabilitation, based on availability and immediate need. Consequently, *usual care* is highly variable and rarely involves a systematic or structured approach to training.

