**8.2 Clinical Outcomes**

***8.2.1 Primary analysis:*** Post-treatment WST skill *capacity* scores will be compared in the experimental and control groups using analysis of covariance (ANCOVA), controlling for baseline score as a covariate.^70^ Borm et al.^71^ demonstrate that correlation between pre- and post-intervention scores (ρ) influences analysis power; when ρ > 0.5, change score is more powerful than direct post-intervention comparison. However, when ρ lies between 0.2 and 0.8, ANCOVA (controlling for baseline score) further reduces the required sample size by 10-40% over change score. Given that preliminary data suggest ρ ~ 0.5,^72^ ANCOVA should provide the most powerful analysis, in addition to reducing error variance and allowing modification when statistical assumptions are not met.^73^ Unequal cell sizes will be accommodated using Method 1 adjustment^74^ and diagnostic assessments made for model assumptions. Significance testing (*p*) and marginal means with 95% confidence intervals will be estimated. Effect size (partial η^2^) will be calculated as a ratio of the effect and total sums of squares, with a 95% confidence interval . To preserve prognostic balance, primary analysis will be based on intention-to-treat; however, since one objective is to estimate the treatment effect, secondary analysis on a per-protocol basis (subjects who adhere to treatment) will also be conducted for comparison.^75^

***8.2.2 Secondary analysis:*** ANCOVA will be used to compare post-treatment scores between the experimental and control groups for WST skill **safety** scores as well as for wheelchair **confidence** (WheelCon) scores and **mobility** (LSA). In each case, baseline score will be used as a covariate. Subjects’ **satisfaction with performance** of meaningful activities (WhOM score) will be analyzed using analysis of variance (ANOVA). Mean administration time for the HUI will be calculated and a preliminary evaluation of change in the treatment group (paired sample *t-test*) will be conducted.

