Previously published studies have used younger or mixed age populations and data specific to older adults are not available. We obtained permission to use a data subset (adults > 50 years) from a yet-to-be published study^72^ providing WST change scores following training and powered our study to capture a comparable change (*m* = 9.3%; *s* = 9.5%). A difference of 9.3% corresponds to acquisition of 3 additional skills on the WST; previous studies report subjects’ perceptions of a *clinically important difference* with such improvements.^17, 18^ In fact, the skills performed on the WST are sequenced from simple (e.g. rolling forwards) to moderate (e.g., propelling on carpet) to complex (e.g., ascending 10° ramp). Research literature reporting on MWC use among older adults specifically implicates carpet, inclines, curbs, gravel and poor sidewalk conditions as barriers to independent mobility.^7^ Acquisition of **even one of these important skills** could quite reasonably represent a minimally clinically important difference (MCID) to wheelchair users, their caregivers, and those providing training. No formal MCID has been established for the WST; however, using data from a Canadian trial,^18^ a Smallest Detectable Difference calculation suggests a difference of 9.2% would exceed any measurement error or noise.^84^ A Reliability Change Index calculation indicates 3.0% is the Minimal Detectable Change required and is a reasonable proxy for MCID^84^ (details in Appendix Q).

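### The planned effect size is an uncorrected eta-squared with a formula that does not match its name; with 30 to 40 completers it overstates its own population value and should not alone size the next RCT

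*Combined protocol and SAP*

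**What the plan says.** The Overview explains that the sample size rests on the primary clinical outcome so that the trial can "provide a reasonable estimate of an effect size for planning the subsequent large scale RCT". Section 8.2.1 compares post-treatment WST capacity "using analysis of covariance (ANCOVA), controlling for baseline score as a covariate". On the statistic it says: "Effect size (partial η^2^) will be calculated as a ratio of the effect and total sums of squares", and it asks for a 95% confidence interval on that ratio. The same section adds: "Significance testing (*p*) and marginal means with 95% confidence intervals will be estimated".

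No bias-corrected form (epsilon-squared, omega-squared or an adjusted eta-squared) is mentioned. The document text gives no rule for turning any of these estimates into the sample size of the next RCT. The adjusted between-group difference and the residual SD are not named as outputs, although the difference follows directly from the marginal means.

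**The concern.** There are two separate defects in one sentence.

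First, a sample eta-squared counts chance variation between arms as effect. It cannot be negative, and its expected value is above zero even when training does nothing. With few error degrees of freedom this is not negligible.

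Second, name and formula disagree. In a model with a baseline covariate, partial eta-squared is effect over effect plus error. Effect over total keeps the variance explained by baseline in the denominator and gives a smaller number.

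An effect-size estimate is a stated product of this trial. If the reported value is carried into a power calculation, both the bias and the ambiguity pass into the next RCT's sample size. The relative bias grows as the true effect shrinks. A difference below 9.3 points is possible: section 8.4 takes 9.3 from change scores after training and does not say that control change was subtracted, while the Background reports "15-20% in intervention groups versus 3-8% in control groups on the WST". This is only conditional, because those same figures imply gaps between arms of 15 − 8 = 7 to 20 − 3 = 17 points.

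**Working it through.** **Inputs.** Difference 9.3 and SD 9.5 (section 8.4: "powered our study to capture a comparable change (*m* = 9.3%; *s* = 9.5"); correlation 0.5 (section 8.2.1: "Given that preliminary data suggest ρ ~ 0.5"); alpha 0.10, power 90%, 15 evaluable per group and 40 enrolled (section 8.4). At a correlation of 0.5 the SD of change equals the SD of the post score, so 9.5 serves for both.

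**The plan's own figure.** Per group: 2 × (1.645 + 1.282)² × (9.5/9.3)² = 17.87. Multiplying by 1 − 0.5² = 0.75 gives 13.40, rounded up to 14, or 15 with one extra subject per group. Exact ANCOVA power is 89.7% at 14 and 91.5% at 15. Then 30/0.75 = 40. The plan's 15 and 40 are reproduced with a two-sided test; sidedness is not stated.

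**Population values at 9.3 points.**
- Between-arm variance: 9.3²/4 = 21.62.
- Residual variance: 9.5² × 0.75 = 67.69.
- Partial eta-squared: 21.62/(21.62 + 67.69) = 0.242.
- Effect over total: 21.62/(21.62 + 90.25) = 0.193.

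**Bias under no effect (closed form).** The partial ratio has mean 1/(1 + error df), with error df = N − 3. That is 1/28 = 0.036 at N = 30 and 1/38 = 0.026 at N = 40.

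**Bias with an effect** (simulated ANCOVA, normal scores, single baseline, no site term, correlation 0.5):

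| True difference | Population partial | Mean partial, N = 30 | Mean partial, N = 40 |
|---|---|---|---|
| 4.5 | 0.070 | 0.101 | 0.093 |
| 6 | 0.117 | 0.146 | 0.138 |
| 9.3 | 0.242 | 0.266 | 0.259 |

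The effect-over-total ratio is also above its own population value of 0.193 at 9.3 points (means 0.210 and 0.205), but both means lie below the population partial value of 0.242.

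**What a correction does.** Partial epsilon-squared = (SS_effect − df_effect × MS_error)/(SS_effect + SS_error). With one effect df this equals eta² − (1 − eta²)/error df. At the means for 9.3 points: 0.266 − 0.734/27 = 0.239 (N = 30) and 0.259 − 0.741/37 = 0.239 (N = 40), against 0.242. Nearly all the bias goes.

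**Consequence for the next RCT.** Assume two-sided alpha 0.05 and 90% power, so total N = (1.960 + 1.282)² × (1 − eta²)/eta² = 10.51 × (1 − eta²)/eta². Entering the mean estimates from a pilot with N = 30:

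| True difference | Correlation | N needed | Partial, mean estimate | Effect over total, read as partial |
|---|---|---|---|---|
| 9.3 | 0.5 | 33 | 29 | 40 |
| 9.3 | 0.3 | 40 | 35 | 40 |
| 9.3 | 0.7 | 22 | 20 | 40 |
| 6 | 0.5 | 79 | 61 | 83 |
| 4.65 | 0.5 | 132 | 90 | 122 |
| 3 | 0.5 | 316 | 150 | 204 |

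The fourth column is always too small. The last is too large, about right or too small, depending on the true effect and the correlation.

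**Mean against typical pilot.** N is strongly nonlinear in eta-squared, so converting a mean overstates the usual shortfall. At 4.5 points with N = 30, the N needed is 140 and the median N across pilots is:
- 128 from partial eta-squared;
- 243 from partial epsilon-squared, which is zero or negative in 31% of pilots;
- 138 from the adjusted difference d and residual SD s, using N = 4 × 10.51 × s²/d².

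**The case against.** A reader might infer that the next RCT would be too small whichever denominator is used. The documents do not support that. With the ratio that section 8.2.1 actually writes, baseline variance in the denominator outweighs the upward bias at the plan's own inputs, and an ANCOVA calculation fed with it gives about 40 subjects where 33 are needed. It gives too few for small effects, or if it is used to size an unadjusted comparison (about 40 against 44 at 9.3 points).

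Three further objections have force.
- Noise exceeds bias. At 9.3 points and N = 30 the sampling SD is about 0.13 against a bias of 0.024, and sizing on a correctly computed partial eta-squared gives too small an RCT in only 53 to 55% of pilots across 4.5 to 9.3 points.
- No section says that partial eta-squared is the sizing input. Marginal means and 95% confidence intervals are already planned, and this trial was itself sized from a difference in points, an SD and a correlation.
- A corrected ratio is no sound sole sizing input either, as the median of 243 against 140 shows.

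These points limit the consequence. They do not remove the bias or the mismatch between name and formula. Nor is the offset from the total sum of squares a safeguard: it is accidental, and it disappears as soon as the formula is made to match the name.

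**Conclusion.** The point holds in limited form. The effect size in section 8.2.1 is uncorrected and, with 30 to 40 completers, biased upward against its own population value. For effect over effect plus error the bias is about +0.024 and +0.017 at 9.3 points, about +0.03 and +0.02 at 4.5 points, and +0.036 and +0.026 under no effect (N = 30 and 40). Separately, the formula does not define the statistic named. At the plan's inputs it averages about 0.21 where the population partial value is 0.24.

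No single direction of error in the next sample size can be asserted. The practical effect is small at 9.3 points and larger in relative terms for smaller effects. The figures rest on SD 9.5, correlation 0.5 unless varied, normal scores and a single baseline measurement. The next-RCT figures also rest on an assumed two-sided alpha of 0.05 and 90% power.

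**What to change.** In section 8.2.1:

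1. Define partial eta-squared as the effect sum of squares over effect plus error sums of squares.
2. Report partial epsilon-squared or partial omega-squared beside it, and leave negative values as they are.
3. Report the ANCOVA-adjusted WST difference with its 95% confidence interval, and the residual SD.
4. State that the next RCT will be sized from the quantities in item 3, not from any eta-type ratio alone.

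This costs one corrected definition, one added formula and a sentence on intended use; no further data are needed. The reported effect size will be slightly smaller and can be negative. Item 4 does not remove the sampling noise of a pilot of this size, so the confidence interval has to be carried into planning with the point estimate.

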**Secondary Objectives: Clinical Outcomes**

1. Evaluate the effect of EPIC WheelS on wheelchair skill capacity and obtain an estimate of the treatment effect size;
2. Evaluate the effect of EPIC WheelS on wheelchair skill safety, wheelchair confidence, satisfaction with activity performance, mobility, and health-related quality of life.

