**8.4 Sample size justification*.*** To address the feasibility outcomes, the number of subjects is large enough to represent the target population and assess the feasibility criteria.^69^ In addition, the sample size is powered to detect a statistically significant difference between groups and provide a reasonable estimate of a treatment effect. The sample size calculations are based on the primary *clinical* outcome (WST), as this will be used in subsequent EPIC WheelS studies. Research in the field of wheelchair skills training is still maturing, with 3 published studies using actual users, and given the novel home program approach an ∝ of .10 was selected to ensure a potentially beneficial treatment effect does not go undetected (Type I error rate). To minimize the risk of identifying such an effect merely by chance (Type II error), the study is powered at 90%. Based on a sample size calculation formula for ANCOVA in RCT designs^71, 83^ each group would require 15 subjects (see Appendix Q for details). In previous Canadian trials, a 9-18% dropout rate has been reported; conservatively adjusting for a 25% dropout rate, a total study N of 40 is planned (n = 20 for each group).

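### Section 8.2.1 names the effect size partial η² but gives the formula for classical η²; computed literally, the reported value would be about 20% too low at the plan's own inputs

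*Combined protocol and SAP*

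**What the plan says.** Section 8.2.1 compares post-treatment WST capacity between groups "using analysis of covariance (ANCOVA), controlling for baseline score as a covariate". It plans a significance test, marginal means with 95% confidence intervals, and an effect size labelled partial η² with its own 95% confidence interval. That effect size "will be calculated as a ratio of the effect and total sums of squares". Nothing else in the document defines the measure or limits the total to a covariate-adjusted total.

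The effect size has a declared use. The rationale in the Overview says the sample size rests on the primary clinical outcome "to provide a reasonable estimate of an effect size for planning the subsequent large scale RCT". The secondary objectives include a commitment to "obtain an estimate of the treatment effect size". The same rationale also says that feasibility is the main intent, and the primary objectives are feasibility objectives.

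**The concern.** The name and the formula describe two different statistics. Effect over total is classical η². Partial η² leaves the covariate's share out of the denominator. The two agree only if baseline explains none of the outcome variance, whereas Section 8.2.1 chooses ANCOVA because it expects baseline to explain a useful part.

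Two analysts following the sentence in good faith, one by its label and one by its formula, could report different values and different intervals. What is at stake is the reported η² and, if a planner took it at its label, the size of the next trial. Power calculations for ANCOVA that start from partial η² convert it to f² on the assumption that covariate variance has already been removed.

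**Working it through.** **Inputs**
- Difference 9.3 and SD 9.5: Section 8.4, which "powered our study to capture a comparable change (*m* = 9.3%; *s* = 9.5"%). The SD is given for change scores. It equals the SD of a single score only if ρ = 0.5 and the pre and post variances are equal.
- ρ: Section 8.2.1 states that "preliminary data suggest ρ ~ 0.5". It also discusses a range: "when ρ lies between 0.2 and 0.8, ANCOVA (controlling for baseline score) further reduces the required sample size by 10-40% over change score". I use 0.2 to 0.8 for sensitivity.
- Alpha 0.10, power 90%, 15 per group, 25% dropout, N = 40: Section 8.4. Sidedness is not stated.
- Allocation 1:1: Methods, Research Design.

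**Step 1. Reproduce the plan's sample size.** With two-sided alpha 0.10 and 90% power:
- Unadjusted n per group = 2 × [9.5 × (1.645 + 1.282) / 9.3]² = 17.87.
- Times (1 − ρ²) = 0.75: 13.40, so 14 per group, or 15 with one extra subject per group.
- 15 / 0.75 = 20 per group, 40 in total.

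This agrees with the plan, so the inputs are being read as the plan used them. One-sided alpha 0.10 would give 11 (12 with the extra subject), which does not match.

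**Step 2. Direction.** With the group effect adjusted for baseline, SS_group + SS_error equals the residual sum of squares of the model with baseline alone. That cannot exceed SS_total. So the ratio as written can never exceed partial η², and it is lower whenever baseline explains any variance.

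**Step 3. Size at the plan's inputs.** Variance components per subject under 1:1 allocation:
- Effect: 9.3² / 4 = 21.6
- Covariate: 9.5² × 0.5² = 22.6
- Error: 9.5² × (1 − 0.5²) = 67.7

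Partial η² = 21.6 / (21.6 + 67.7) = **0.242**.
As written = 21.6 / (21.6 + 22.6 + 67.7) = **0.193**.
Shortfall = 1 − 0.193/0.242 = 20%.

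In 20,000 simulated ANCOVAs at each sample size, the median partial and as-written values were 0.259 and 0.199 with 15 per group, and 0.254 and 0.198 with 20 per group. The as-written value never exceeded the partial value.

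**Step 4. Effect on a later sample size, if the value is taken as partial η².** With f² = η² / (1 − η²):
- Partial: 21.6 / 67.7 = 0.319
- As written: 21.6 / 90.25 = 0.240
- Ratio: 0.319 / 0.240 = 1.33, which is 1/(1 − ρ²) at ρ = 0.5

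To illustrate, assume two-sided alpha 0.05 and 90% power for the next trial; the documents state neither for it. Total N ≈ (1.960 + 1.282)² / f² = 10.51 / f². That gives 32.9 (33) from the partial value and 43.9 (44) from the as-written value.

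**Step 5. Sensitivity to ρ**, holding the single-score SD at 9.5:

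| ρ | Partial η² | As written | Shortfall | N inflation |
|---|---|---|---|---|
| 0.2 | 0.200 | 0.193 | 3% | 1.04 |
| 0.3 | 0.208 | 0.193 | 7% | 1.10 |
| 0.5 | 0.242 | 0.193 | 20% | 1.33 |
| 0.7 | 0.320 | 0.193 | 40% | 1.96 |
| 0.8 | 0.400 | 0.193 | 52% | 2.78 |

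If 9.5 is instead held as the change-score SD, the single-score SD is 9.5 / √(2(1 − ρ)). The pairs become 0.285 and 0.277 at ρ = 0.2, and 0.210 and 0.087 at ρ = 0.8. The inflation factor is unchanged, because it depends on ρ alone.

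**The case against.** The case for leaving the sentence alone has several parts.

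*The total may be loose shorthand for effect plus error, as the label suggests.* That is possible, and the reported statistic would then be right. The text does not say so, and read literally it defines a different quantity. This is why the understatement is conditional on literal computation.

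*The next trial may never use η².* This stands. The only planning method the document shows takes a difference, an SD and ρ. Nothing says that η² will be fed into a power calculation. A reader might infer that the next RCT will be oversized by a third; the documents support only that it could be, if the mislabelled value is used as partial η².

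*The plan already provides most planning inputs.* Largely true. Section 8 promises group means and SDs, and Section 8.2.1 adds marginal means with intervals and a p-value, from which the adjusted difference and its interval can be recovered. Stating them outright is reporting advice and does not correct an error.

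*The error is conservative and small beside sampling noise.* By the noncentral F method, an observed partial η² of 0.242 has a 95% interval of about 0.02 to 0.46 with 30 analysed and 0.04 to 0.43 with 40. A shift of 0.05 lies well inside either. But the shift has a fixed direction, and its size depends on ρ, so it is not a chosen safety margin.

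*The effect size is not the trial's main product.* Correct. A reader might infer that the error undermines the trial's central deliverable. The effect size is a stated aim, but the document puts feasibility first and lists this estimate among the secondary objectives.

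**Conclusion.** The label and formula in Section 8.2.1 contradict each other, and the sentence is wrong as written. Followed literally, it yields classical η² and an interval for classical η², both under the name partial η². The point estimate is about 20% low at the plan's inputs. That figure rests on ρ near 0.5 and on treating 9.5 as the SD of a single score, which holds only under equal variances at that ρ. The later inflation of N by 1.33 (range 1.04 to 2.78 over ρ from 0.2 to 0.8) needs the further step of using the value as partial η². The example of 44 against 33 also rests on an assumed alpha and power.

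The documents do not support reading this as a flaw in the primary analysis. The ANCOVA, its p-value, the adjusted means and their intervals, and the N of 40 do not depend on how η² is defined. Severity is minor to moderate: a definitional error in a quantity the trial sets out to report.

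**What to change.** In Section 8.2.1, replace the definition with: partial η² = SS_group / (SS_group + SS_error), taken from the ANCOVA, with its 95% confidence interval based on the same definition. Keeping the total in the denominator and renaming the measure η² would also remove the contradiction, but the first option matches the measure the plan names and is the form that ANCOVA-based planning uses.

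It would help to add, as planning outputs, the adjusted mean difference in WST points with its 95% confidence interval, the residual SD and the observed pre-post correlation. These are the kinds of quantities used by the plan's own sample-size method.

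The cost is one corrected sentence and, if the addition is accepted, one more. No extra data are needed, and the added outputs come from data and a model already planned.

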**Methods**

**
[figure not shown]
1. Research Design.** This 2-year feasibility study will use a two-site (Winnipeg and Vancouver) randomized controlled trial to compare differences in older adults’ wheelchair mobility skills with EPIC WheelS versus usual care. Subjects will be randomly assigned to the experimental group (usual care + EPIC WheelS) or a control group (usual care only) using a 1:1 allocation ratio between groups. To support balance between groups and masking of assignment, a central computerized randomization process will be designed by our team statistician ([name]), with an undisclosed block size and stratified by site (Winnipeg *n* = 20; Vancouver *n* = 20). Once subjects are enrolled, the Study Tester will collect baseline data and enter them into a secure database. The Site Coordinator will contact [name] via telephone or email and obtain group assignment within 48 hours. Subject contact information will be forwarded to the appropriate group Trainer to arrange for an initial training session or social visit. To address bias, subjects will be instructed not to discuss their program and Study Testers will be blinded to group allocation.

Experimental group subjects will attend 2 training sessions with an expert Trainer. The Trainer will individualize a structured home training program, delivered via a computer tablet, and subjects will train for 1 month. The Trainer will make telephone contact at the end of weeks 1 and 3. Control group subjects will receive 2 social visits to address attention balance through exposure to study personnel. In addition, they will be provided with a similar computer tablet with cognitive training games to account for tablet device and activity exposure.

**2. Assessments.** The clinical outcome measures will be collected at baseline (pre-randomization) and post-intervention. A 1-month intervention will provide ≥ 8 hours of training, which is comparable to clinical studies using the WSTP where a significant improvement in skill capacity was observed.^17-19^

**3. Subjects.** A total of 40 community-dwelling MWC users living in Winnipeg and Vancouver (20 at each site) will be recruited on a volunteer basis (see Section 8.1 for sample size justification). To optimize the impact of the treatment, individuals with less than one year of MWC use will be recruited as they are still developing routines and patterns of wheelchair use and potentially more amenable to adapting their mobility techniques.^12^

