***4.2.2 Secondary measures***

Secondary clinical outcomes reflect more distal impacts of the intervention. Given the dearth of evidence in the literature, there is substantial value in understanding the relationship between skill acquisition and safety, confidence, community participation, mobility and utility. The secondary measures will contribute to discerning a *clinically* important impact of the EPIC WheelS intervention.

***4.2.2.1 WST Skill Safety****.* The WST also provides a total Skill Safety score (0-100%) reflecting the number of skills addressed in a safe manner, regardless of whether the skill is passed or not (see Appendix I). This is of considerable importance since training also involves learning to recognize risks and limitations. Recognition that a particular situation is unsafe or that one is not capable of safely performing an activity is vastly preferable to attempting a maneuver that may lead to accident or injury.

***4.2.2.2 Wheelchair Outcome Measure* (WhOM).** The rehabilitation literature strongly suggests that intervention outcomes should include not only externally defined measures, but also measures of *user-identified* activities of relevance and perceived satisfaction with performance.^41-43^ A 2008 review of wheelchair-specific outcomes found the WhOM was the only tool that included activities selected and weighted by the user and featured participation in social roles.^44^ Using an interview format, MWC users identify relevant activities and rate them on both Importance and Satisfaction, using an 11-point scale (0-10) (See Appendix J). The WhOM demonstrates good reliability (Test-retest ICC = 0.83-0.88; Inter-rater ICC = 0.90-0.91) and validity (correlations with LIFE-H: *r_s_* = 0.3-0.5) in use among individuals with SCI^45^ and older adults (Test-retest ICC = 0.77–1.00; correlation with QUEST *r_s_* = 0.36 -0.45).^46^ As part of the baseline data collection, the five most important activities identified with the WhOM will be used to customize the training program for experimental group subjects.

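### WhOM satisfaction is assigned an unspecified ANOVA with no stated baseline covariate, although its baseline is collected and every other between-group clinical outcome uses baseline-adjusted ANCOVA (minor)

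*Combined protocol and SAP*

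**What the plan says.** For the primary outcome, WST capacity, Section 8.2.1 compares post-treatment scores "using analysis of covariance (ANCOVA), controlling for baseline score as a covariate". It defends that choice on power and on reduced error variance.

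Section 8.2.2 carries the method over to three secondary outcomes: "ANCOVA will be used to compare post-treatment scores between the experimental and control groups for WST skill" safety, and likewise for WheelCon and LSA. It adds: "In each case, baseline score will be used as a covariate". The sentence on WhOM then changes method; satisfaction with performance "of meaningful activities (WhOM score) will be analyzed using analysis of variance (ANOVA". Nothing more is said about that model. HUI3 is not compared between groups; for it, "a preliminary evaluation of change in the treatment group (paired sample *t-test*) will be conducted".

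The baseline WhOM score will exist. Methods, item 2 (Assessments) states: "The clinical outcome measures will be collected at baseline (pre-randomization) and post-intervention". Section 4.2 repeats baseline and 1 month for the clinical outcomes. Section 4.2.2.2 describes the rating ("MWC users identify relevant activities and rate them on both Importance and Satisfaction, using an 11-point scale (0-10") and places WhOM at baseline: "As part of the baseline data collection, the five most important activities identified with the WhOM" are used to customise training in the experimental arm.

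**The concern.** WhOM is the only between-group clinical outcome for which the plan does not state baseline adjustment, and the reasons given in 8.2.1 for preferring ANCOVA are not specific to the WST. If the ANOVA is on post scores, variation explained by the baseline stays in the error term, and a chance baseline difference passes partly into the estimated effect. If it is on change scores or group by time, the baseline is used, but with its coefficient fixed at 1 instead of estimated.

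The Overview sets effect sizes for the primary and secondary measures as a deliverable for planning the larger RCT, and satisfaction with activity performance is a named secondary objective. As written, the WhOM effect would be estimated less precisely than it could be, and on a different footing from the other measures. Because the model is not specified, the choice among three ANOVAs also stays open until data are in hand.

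**Working it through.** **Inputs from the documents**
- Section 8.4: alpha 0.10, power 90%, 15 per group before dropout, 25% dropout, N = 40; WST difference 9.3, SD 9.5.
- Section 8.2.1: pre-post correlation (rho) about 0.5, given in the WST analysis.
- For WhOM: no SD, effect or pre-post correlation. Section 4.2.2.2 gives only reliability and validity coefficients.

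**Reproducing the plan's own figure (WST)**
- Unadjusted n per group = 2 × (9.5/9.3)² × (1.645 + 1.282)² = 17.87, so 18.
- With ANCOVA at rho 0.5: 17.87 × (1 − 0.25) = 13.40, so 14, or 15 with one extra subject per group.
- Dropout: 15 / 0.75 = 20 per group, N = 40.

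The stated design reproduces with two-sided alpha. The SD of 9.5 is described as that of change scores; at rho 0.5 and equal variances the change and post SDs coincide, because √(2(1 − 0.5)) = 1. The plan has therefore already counted on the ANCOVA saving for the WST (18 down to 14 or 15).

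**Variance of the WhOM treatment effect, ANCOVA relative to ANOVA**

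Large-sample ratios, assuming equal baseline and post variances for the change score:
- against post-only ANOVA: 1 − rho²
- against change-score ANOVA: (1 + rho)/2. With two time points, the group-by-time test is equivalent to this.

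Estimating the baseline slope costs something in small samples. With 30 completers the expected inflation is 1 + 1/(30 − 4) = 27/26 = 1.038. Multiplying it in:

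| Assumed rho | ANCOVA / post-only | Cut | ANCOVA / change | Cut |
|---|---|---|---|---|
| 0.3 | 0.91 × 1.038 = 0.945 | 5.5% | 0.65 × 1.038 = 0.675 | 32.5% |
| 0.5 | 0.75 × 1.038 = 0.779 | 22% | 0.75 × 1.038 = 0.779 | 22% |
| 0.7 | 0.51 × 1.038 = 0.530 | 47% | 0.85 × 1.038 = 0.883 | 12% |

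A bivariate-normal simulation at 15 per arm agrees with these cuts to within about one percentage point. At rho 0.5, either ANOVA needs 1/0.779 = 1.28 times as many subjects for equal precision.

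**Where the advantage ends.** At this size ANCOVA beats post-only when (1 − rho²) × 27/26 < 1, that is rho above √(1/27) = 0.19. It beats the change score when (1 + rho)/2 × 27/26 < 1, that is rho below 25/27 = 0.93.

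**Width of the interval (normal approximation, SD units).** Post-only: 1.96 × √(2/15) = 0.72. ANCOVA: 0.716 × √0.945 = 0.70, 0.716 × √0.779 = 0.63 and 0.716 × √0.530 = 0.52 at rho 0.3, 0.5 and 0.7.

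**Chance imbalance in a post-only comparison.** The standard error of the baseline difference is √(2/15) = 0.37 SD. An imbalance of that size carries rho × 0.37 = 0.18 SD into the unadjusted comparison at rho 0.5.

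**The case against.** The strongest reply is that the plan says only ANOVA. A reader might infer that the baseline score is discarded, but the text does not say so: a change-score or group-by-time model would use it. That stands, and the point is therefore worded as no stated covariate and an unspecified model. It does not remove the point, since those two models are also expected to be less precise than ANCOVA over the range shown.

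A second reply is that randomisation keeps an unadjusted comparison unbiased on average, and that Section 8 plans a qualitative look at balance and prognostic importance. Both are true. The loss is in precision and, for a post-only model, in exposure to chance imbalance; inspecting balance does not recover either.

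Third, a reader might apply the WST correlation of about 0.5 to WhOM and quote the large-sample penalty of 1/0.75, or 33% more subjects. The documents give that correlation for the WST only, and at 15 per arm the penalty is about 28%. At rho 0.3 the gain over post-only is small. Fifteen per arm is also the plan's conservative case: the 9–18% dropout quoted in 8.4 would leave about 16 to 18 (20 × 0.82 = 16.4; 20 × 0.91 = 18.2). That barely moves the cuts (22% to 23% at rho 0.5).

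Finally, since subjects choose their own activities, one might argue either that baseline satisfaction will vary widely or that adjustment is inappropriate. The documents support neither: they give no WhOM spread, and each subject still has a baseline satisfaction rating.

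**Conclusion.** The point holds as a minor one. Section 8.2.2 departs, without a stated reason, from the baseline-adjusted ANCOVA used for the four other between-group clinical outcomes, and it leaves the WhOM model undefined although the covariate will be available. The size depends on a WhOM pre-post correlation that the documents do not give. Over the assumed range of 0.3 to 0.7, the variance reduction from ANCOVA runs from slight to nearly half against post-only ANOVA, and from about a third down to about an eighth against change-score ANOVA. These figures assume 15 completers per arm, roughly normal scores and, for the change score, equal variances at the two visits.

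The documents do not support reading this as a source of bias, nor as a threat to the primary analysis or to the feasibility decisions. It affects one secondary effect estimate in a trial sized on the WST.

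**What to change.** In Section 8.2.2, replace the ANOVA for WhOM with ANCOVA of post-treatment WhOM satisfaction on treatment group, with baseline WhOM satisfaction as covariate, in line with the other secondary outcomes. The cost is one sentence and one degree of freedom, with no new data.

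Site, the stratification factor, may be added for one further degree of freedom. It is optional: no other model in Section 8.2 includes it, so adding it for WhOM alone would create a new difference between outcomes.

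If the sponsor prefers to keep ANOVA, the plan should state the dependent variable (post score, change score or group by time) and the reason. Either way, it would help to say whether the post-treatment ratings refer to the activities named at baseline; the text available does not, and the pre-post correlation depends on it.
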